## Abstract

**Background:**

As a central nervous system disease, migraine often coexists with gastrointestinal disorders, which suggests a disruption of brain-gut regulation. Clinical studies have confirmed that acupuncture and flunarizine not only alleviate migraine attacks but also substantially inhibit accompanying gastrointestinal symptoms. However, it is still not clear how acupuncture and flunarizine regulate the interactions of brain, gut, and microbiome. Therefore, this study will combine neuroimaging technology and gut microbiota detection technology to explore and compare the effects and brain-gut modulating mechanisms of acupuncture and flunarizine for migraine.

**Methods:**

This randomized clinical trial will recruit 66 patients with migraine without aura. Participants will be randomly assigned in a 1 : 1 ratio to an acupuncture group or a control group. The acupuncture treatment strategy is based on experience from our previous study and consensus meetings with clinical experts. Patients will receive 12 sessions of manual acupuncture treatment (once every other day to a total of three times per week, followed by a 2-day break). Flunarizine will be administered at a dose of 5 mg daily in the control group. Participants in both groups will receive treatment for a period of 4 weeks. The primary outcome is the change in frequency of migraine attacks, and the secondary outcomes include the changes in migraine days (days on which migraine attacks occurred), average migraine severity, gastrointestinal symptoms, psychiatric symptoms, and quality of life. Fresh stool samples will be collected, and 16S ribosomal RNA gene sequencing analysis will be used for gut microbiota. Magnetic resonance imaging will be applied to detect between-group changes in brain function. The abovementioned indicators will be collected at baseline, after a 4-week intervention, and at the 12-week follow-up. *Discussions.* From the perspective of brain-gut regulatory mechanisms, we will combine brain neuroimaging and gut microbiological data to partially reveal the similarities and differences of acupuncture and flunarizine on the treatment of migraine. The trial is registered with ChiCTR2000034417.

## 1. Introduction

Migraine is a neurological disorder characterized by recurrent attacks, high clinical incidence, and obvious disability. A latest systematic analysis of the Global Burden of Disease study reported that 1.25 billion people suffered from migraine in 195 countries and territories [1]. Migraine ranked second globally in terms of years lived with disability [2] and was the leading cause of disability for individuals at the age of younger than 50 years [3]. Migraine increases the risk of cardiovascular and cerebrovascular diseases [4–6] and may even lead to self-harm and suicide in severe attacks [7], which brings extensive negative impacts to patients' physical and mental health.

Previous studies have found that migraine attacks can be triggered by foods such as alcohol, chocolate, and cheese [8], and the number of headache days and episodes are greatly reduced during fasting periods [9], indicating that migraine is associated with the disruption of brain-gut interactions [10]. Migraine often coexists with gastrointestinal disorders [11, 12], commonly accompanied by nausea, vomiting, and other gastrointestinal symptoms [13, 14], which suggests that the gut microbiota may play a key role in migraine via brain-gut interactions [15]. Migraine attacks can alter gut microbiota composition [16], while gut microbiota may be related to migraine pathogenesis [17]. Several studies have shown that probiotics are effective in reducing the intensity and frequency of migraine attacks and may substantially reduce the consumption of medication and the incidence of migraine disability [18, 19]. Moreover, the traditional Chinese herb *Gastrodia elata*, which is often used to treat headache or migraine, has been reported to promote migraine relief and modulate gut microbiota [20]. A report released by the Rome Working Team has confirmed that brain-gut interactions are associated with changes in the neural, endocrine, and immune pathways [21]. On the basis of the abovementioned evidence, we suggest that there is an interaction between the brain and the gut in migraineurs.

Pharmacological and nonpharmacological therapies have been used to prevent migraine attacks. The calcium channel blocker flunarizine, which is recommended as a first-line prophylactic medication in several guidelines [22–25], has been shown to be effective in relieving gastrointestinal manifestations in addition to reducing the frequency and duration of migraine attacks [26–28]. In terms of nonpharmacological therapy, acupuncture has been widely recognized as an effective treatment for migraine prophylaxis [29]. As acupuncture has beneficial effects and mild side effects [30], migraineurs have expressed good compliance and high satisfaction with acupuncture therapy [31, 32]. Our previous studies have confirmed that acupuncture treatment has a good effect on relieving migraine attacks and digestive symptoms [33, 34]. There is evidence that acupuncture can regulate gut microbiota disorders and improve the diversity and richness of bacteria species in the gut [35, 36]. Several lines of research on the use of acupuncture and flunarizine for migraine have shown that flunarizine has a good effect in reducing pain intensity and improving quality of life, and in addition to the effects mentioned above, acupuncture can effectively reduce the number of migraine days and regulate psychological state [37, 38].

Previous studies have revealed substantial abnormalities in brain functional activities and in the species diversity and metabolic functions of gut microbiota in migraine patients compared with healthy controls [15, 39]. However, there is no report on whether clinical symptoms are relieved by medication and acupuncture is related to the regulation of brain-gut-microbiota interactions in migraineurs to date. Therefore, using neuroimaging and gut microbiota examination, we aim to examine the effect of acupuncture and flunarizine treatment for migraine and compare the similarities and differences in gut microbiota and brain functional network elicited by acupuncture and flunarizine treatment. Furthermore, a tripartite network analysis based on graph theory will be used to explore the relationships among brain network activities, gut microbiota, and clinical efficacy under the acupuncture and flunarizine for migraineurs.

## 2. Methods and Design

### 2.1. Objectives

This study aims to (1) re-evaluate the efficacy of acupuncture and flunarizine on migraine treatment; (2) compare the similarities and differences in brain activity and gut microbiota associated with acupuncture and flunarizine treatment for migraine; and (3) investigate the correlation between symptom improvement, brain activity changes, and gut microbiota regulation elicited by acupuncture and flunarizine.

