### 2.2. Trial Design

Study participants will be patients who have migraine without aura (MwoA). A total of 66 patients meeting the diagnostic criteria of the International Classification of Headache Disorders [40] will be recruited and randomly assigned to two groups (1 : 1 allocation ratio) to receive either acupuncture or drug therapy. This study protocol was developed in accordance with the Standard Protocol Items: Recommendations for Intervention Trials (SPIRIT) [41]. This trial has been registered with the Chinese Clinical Trial Registry (ChiCTR). The flowchart of the trial design is shown in Figure 1.

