#### 2.3.1. Inclusion Criteria

Eligible participants must meet the following criteria: (1) men or women aged 18–55 years; (2) right handed, length of education ≥6 years; (3) a history of migraine of, at least, 1 year with the first onset before the age of 50 years; (4) migraine attacks ≥2 times and number of migraine days <15 days per month during the past 3 months and baseline observation; (5) completion of the baseline headache diary; and (6) provision of written informed consent.

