#### 2.4.1. Clinical Data Collection

All participants will be instructed to complete a headache diary every 4 weeks during the study. The headache diary will mainly record the time of migraine onset, migraine duration, migraine severity (detected by a visual analog scale), and use of rescue medicine.

The following clinical outcomes will be assessed by independent assessors who have been trained before participating in the study. The primary outcome is the change in frequency of migraine attacks, and the secondary outcomes include the changes in migraine days (days on which migraine attacks occurred), average migraine severity, gastrointestinal symptoms, psychiatric symptoms, and quality of life. The intensity and frequency of gastrointestinal symptoms will be assessed using the Gastrointestinal Symptom Rating Scale (GSRS) [42, 43]. As migraine is often accompanied by psychiatric symptoms, the Beck Anxiety Inventory (BAI) [44] and the Beck Depression Inventory (BDI) [45] will be used to measure the emotional states of migraineurs, and quality of life will be assessed using the Migraine-Specific Quality of Life Questionnaire (MSQ) [46].

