Currently, positive control is one of the most commonly used control methods in randomized controlled trials (RCTs). The calcium channel blocker flunarizine, recognized as a first-line treatment for migraine [22–25], is widely used as a comparator in RCTs [37, 75, 76]. This control design is a good way to compare the efficacy, tolerability, and safety of different medical interventions for migraine. The present study is the first one to investigate the brain-gut regulatory mechanisms underlying different interventions (acupuncture versus flunarizine) for migraine.

Therefore, taking the brain-gut regulatory mechanisms as a starting point for this study, we will combine brain neuroimaging and gut microbiological data to analyze the similarities and differences of acupuncture and flunarizine treatment for migraine. This will permit investigation of the correlations between clinical efficacy and changes in gut microbiota and brain network function elicited by acupuncture and flunarizine treatment based on tripartite network analysis. It is hoped that the findings will inform efforts to partially reveal the common and different mechanisms of acupuncture and flunarizine on the treatment of migraine.

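### With two active arms and no untreated or sham reference, the trial can estimate only acupuncture minus flunarizine; change shared by both arms cannot be credited to either treatment

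*Protocol article*

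**What the plan says.** **Design.** Section 2.2 has 66 patients "randomly assigned to two groups (1 : 1 allocation ratio) to receive either acupuncture or drug therapy". Section 2.6.2 and the Discussion present flunarizine as an active (positive) control. No other group is described.

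**Aims.** Section 2.1 lists as objective 1 to "re-evaluate the efficacy of acupuncture and flunarizine on migraine treatment", and as objective 2 to "compare the similarities and differences in brain activity and gut microbiota associated with acupuncture and flunarizine treatment for migraine". The Introduction puts the second aim causally: "compare the similarities and differences in gut microbiota and brain functional network elicited by acupuncture and flunarizine treatment". Objective 3 in section 2.1 uses the same causal verb. The Discussion hopes to "partially reveal the common and different mechanisms of acupuncture and flunarizine on the treatment of migraine".

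**Selection and outcome.** Section 2.3.1 requires "migraine attacks ≥2 times and number of migraine days <15 days per month during the past 3 months and baseline observation". In section 2.4.1, "The primary outcome is the change in frequency of migraine attacks", and section 2.4 makes the 4-week baseline the starting measurement.

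**Planned inference.** The sample size (section 2.5.1), the clinical tests (section 2.9.1) and the comparison of correlation coefficients (section 2.9.4) all address a difference between the two groups. The article does not mention that shared change is uncontrolled.

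**The concern.** The aims reach further than the comparison that randomisation supports. A difference between arms in attacks, taxa or connectivity can be attributed to the choice of treatment. A change that appears equally in both arms cannot, because no group shows what would have happened without treatment.

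Several ordinary sources would move both arms together:

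- the natural course of an episodic disease;
- regression to the mean after selection on recent attacks;
- expectation, since patients in both arms know they are being treated;
- study procedures such as repeat scanning and diary keeping. The diet rule before stool sampling is the weakest of these, because it also applies at baseline.

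At stake is what the trial may conclude. Fewer attacks in both arms would not show that each treatment works. A taxon or connection that moves in both arms would not show a mechanism the two treatments have in common. Those are natural readings of objective 1 and of the *similarities* half of objective 2.

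**Working it through.** **1. The protocol's own figure.** Inputs from section 2.5.1: changes in migraine days of 4.1 ± 3.5 and 1.9 ± 2.3, α = 0.05, power 0.80; two-sided testing from section 2.9.1.

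- Difference = 4.1 − 1.9 = 2.2.
- SD = √((3.5² + 2.3²)/2) = 2.961.
- d = 2.2/2.961 = 0.743.
- A two-sided t test then needs 30 per group (power 0.808), as stated.
- 60 × 1.1 = 66, as stated.

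The size rests only on the difference between arms.

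**2. Shared change drops out.** Let the mean changes be c + a (acupuncture) and c + f (flunarizine), where c is change that would occur without treatment and a and f are specific effects. The randomised contrast is (c + a) − (c + f) = a − f. It holds no information on c. With two arm means and three unknowns, a and f cannot be separated from c. The same algebra applies to a taxon's abundance or a centrality measure. The expected flunarizine change of 1.9 days shows this: at n = 30 its 95% interval is 1.9 ± 2.045 × 2.3/√30 = 1.9 ± 0.86, about 1.0 to 2.8, but nothing in the trial says how much of it is drug effect.

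**3. How easily shared change looks like efficacy of both.** Assumptions: a = f = 0, both arms improve by c migraine days, SDs 3.5 and 2.3, n = 30 per arm, two-sided 5% within-arm t tests. Migraine days are used because they are the only outcome with SDs in the document.

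| c (days) | Acupuncture arm significant | Flunarizine arm significant | Both (product) |
|---|---|---|---|
| 0.5 | 0.114 | 0.209 | 0.02 |
| 1.0 | 0.328 | 0.634 | 0.21 |
| 1.5 | 0.621 | 0.932 | 0.58 |
| 1.9 | 0.820 | 0.992 | 0.81 |

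The document gives no value for c, so this is a range and not a forecast.

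**4. Regression to the mean alone.** The document gives no attack-rate distribution. Assumption: gamma-distributed true monthly rates, mean 2.5 to 4, SD half the mean, Poisson monthly counts, no treatment. The average fall from the baseline month to the next, in attacks per month, depends on how the entry rule in section 2.3.1 is read:

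- at least 2 in the baseline month only: 0.38 to 0.67;
- at least 2 in each of the four months: 0.26 to 0.46;
- an average of at least 2 over the four months: 0.10 to 0.25.

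Overall this is about 0.1 to 0.7. The model leaves out the cap of fewer than 15 migraine days, which selects in the opposite direction. The contribution is modest, and step 2 does not need it. It also says nothing direct about taxa or connectivity, which are not entry criteria.

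**5. Similarity.** At 30 per arm:

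- The 95% interval for a standardised mean difference has half-width 2.00 × √(2/30) = 0.517 SD.
- Power to detect a true difference of 0.5 SD is 48%.
- For the correlation comparison, SE = √(2/27) = 0.272 and tanh(1.96 × 0.272) = 0.488, so r = 0 in one arm and r = 0.48 in the other would not differ significantly.

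A non-significant comparison is therefore compatible with substantial differences.

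**The case against.** **An active control is legitimate.** The article presents flunarizine as an established first-line drug and acupuncture as widely recognised, and objective 1 speaks of re-evaluating efficacy. It can be read as comparative efficacy, which the design serves. That stands. But the wording names the efficacy of both treatments. Relying on flunarizine's known clinical effect would be an outside assumption that the article does not state, and it would not carry over to the brain and gut measures, for which the Discussion calls this the first study of its kind.

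**The promise is hedged.** Objective 2 uses the language of association, and the Discussion speaks of hope and of partial insight. That is fair as to how much is claimed. It does not settle attribution, because the Introduction, objective 3 and the Discussion describe changes as elicited by the treatments.

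**Stronger readings.** A reader might infer that the trial will test change within each arm and report it as efficacy, or will take a non-significant comparison as proof of similarity. The document supports neither: section 2.9.1 plans only between-group clinical tests, and no rule for declaring similarity is given. A reader might also think that selection on recent attacks is what breaks the design. It is not; it adds a modest amount to a problem that exists for any shared change.

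**The analysis plan may deal with it.** An unseen plan may set out how similarity is judged, and the absence of a margin here is not a fault. It cannot supply a missing reference group, and the arms and objectives are fixed in this document.

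**Conclusion.** The point holds as a mismatch between aims and design. The trial can estimate acupuncture minus flunarizine, including differences in brain and gut change and in correlations. It cannot support the efficacy of each treatment, if objective 1 is read that way, nor attribute changes shared by both arms to the treatments as common mechanisms.

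This follows from the two-arm structure and needs no numerical assumption. The figures only show scale: a 58% to 81% chance that both arms look effective under a purely shared improvement of 1.5 to 1.9 migraine days, and a confidence interval of about ±0.52 SD around any between-arm difference. The first rests on the protocol's SDs and an assumed shared change; the second on 30 evaluable patients per arm. The regression-to-the-mean range rests on an assumed attack-rate distribution.

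The randomised comparison, the allocation and the sample-size arithmetic checked here are not called into question.

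**What to change.** 1. State objective 1 as the relative efficacy of acupuncture versus flunarizine.
2. In objectives 2 and 3 and in the conclusions, limit treatment-attributable brain and gut findings to between-arm differences in change.
3. Report within-arm and shared changes as uncontrolled description, without calling them elicited by treatment or common mechanisms, and add a sentence naming the lack of an untreated or sham reference as a limitation.
4. Do not read a non-significant between-arm test as similarity. Report the difference with its 95% confidence interval. Whether to set a similarity margin for exploratory measures can be left to the analysis plan; any margin would have to be wider than about 0.52 SD to be attainable at 30 per arm.

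The cost is rewording, plus confidence intervals from comparisons already planned. No arm, patient or visit is added. The downside is fewer and weaker mechanistic claims.

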### 2.2. Trial Design

Study participants will be patients who have migraine without aura (MwoA). A total of 66 patients meeting the diagnostic criteria of the International Classification of Headache Disorders [40] will be recruited and randomly assigned to two groups (1 : 1 allocation ratio) to receive either acupuncture or drug therapy. This study protocol was developed in accordance with the Standard Protocol Items: Recommendations for Intervention Trials (SPIRIT) [41]. This trial has been registered with the Chinese Clinical Trial Registry (ChiCTR). The flowchart of the trial design is shown in Figure 1.

### 2.3. Participants

All potential MwoA patients meeting the diagnostic criteria will be recruited from the outpatient department of neurology at the Hospital of Chengdu University of Traditional Chinese Medicine (TCM). A recruitment advertisement for this trial will also be posted on the WeChat platform. Only MwoA patients who are completely in conformity with the inclusion criteria will be recruited to the trial.

#### 2.3.1. Inclusion Criteria

Eligible participants must meet the following criteria: (1) men or women aged 18–55 years; (2) right handed, length of education ≥6 years; (3) a history of migraine of, at least, 1 year with the first onset before the age of 50 years; (4) migraine attacks ≥2 times and number of migraine days <15 days per month during the past 3 months and baseline observation; (5) completion of the baseline headache diary; and (6) provision of written informed consent.

#### 2.3.2. Exclusion Criteria

Patients matching any of the following criteria will be excluded: (1) any combination of head trauma history, secondary headache, tension-type headache, intermittent-type headache, cluster-type headache, or cardiovascular and digestive diseases; (2) a history of major intestinal resection or gastrointestinal surgery; (3) presence of psychiatric disease, infection, bleeding disorders, or allergic constitution; (4) pregnancy, lactation, or plans to become pregnant within 6 months; (5) inability to understand or fill in a headache diary; (6) nuclear magnetic contraindications, such as claustrophobia; (7) a history of taking antibiotics or receiving acupuncture therapy for 3 days or more in the past 3 months; (8) long-term use of analgesic drugs and medications to prevent migraine attacks; and (9) participation in a similar study in the last 3 months.

### 2.4. Data Collection

At the 4-week baseline, patient demographic surveys (age, sex, height, weight, education, disease course, and medical history) will be administered. Clinical outcomes, fecal samples, and magnetic resonance imaging (MRI) data will be collected at the 4-week baseline, end of the 4-week intervention, and at the 12-week follow-up (Table 1).

#### 2.4.1. Clinical Data Collection

All participants will be instructed to complete a headache diary every 4 weeks during the study. The headache diary will mainly record the time of migraine onset, migraine duration, migraine severity (detected by a visual analog scale), and use of rescue medicine.

The following clinical outcomes will be assessed by independent assessors who have been trained before participating in the study. The primary outcome is the change in frequency of migraine attacks, and the secondary outcomes include the changes in migraine days (days on which migraine attacks occurred), average migraine severity, gastrointestinal symptoms, psychiatric symptoms, and quality of life. The intensity and frequency of gastrointestinal symptoms will be assessed using the Gastrointestinal Symptom Rating Scale (GSRS) [42, 43]. As migraine is often accompanied by psychiatric symptoms, the Beck Anxiety Inventory (BAI) [44] and the Beck Depression Inventory (BDI) [45] will be used to measure the emotional states of migraineurs, and quality of life will be assessed using the Migraine-Specific Quality of Life Questionnaire (MSQ) [46].

#### 2.4.2. Gut Microbiota Collection

Fecal samples will be collected from 66 MwoA patients at baseline, end of the 4-week intervention, and at the 12-week follow-up. Patients will be instructed to maintain a regular diet and refrain from spicy, oily food, and any food containing probiotics (e.g., yogurt) for 1 week before the fecal sample collection. Migraineurs will receive a teaching video, as well as detailed written and oral instructions, on how to collect feces using a Longseegen stool storage kit (Longsee Medical Technology Co. LTD., Guangdong, China) in the morning after an overnight fast. The collection time of the fecal sample will be ±1 days for MRI examination, and the collection sites can be selected at home or in the hospital according to patients' preference. The inside of the middle section of the feces (approximately 3 g) will be collected and then immediately frozen at −80°C in the hospital or briefly stored in a domestic refrigerator at 4°C before being transferred to researchers within 24 hours for subsequent analysis.

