#### 2.4.3. MRI Data Acquisition

An MRI scan will be carried out using a 3.0TGE Signa MR750 system (GE Healthcare, Milwaukee, USA) in the Hospital of Chengdu University of TCM. High-resolution 3D T1-weighted anatomical images using a 3D spoiled gradient-recalled sequence will be produced. The acquisition parameters are as follows: repetition time (TR)/echo time (TE) = 5.97/1.96 ms, field of view (FOV) = 240 × 240 mm^2^, flip angle = 12°, matrix size = 512 × 512, 156 slices, and voxel size = 1 × 1 × 1 mm^3^.

Resting-state fMRI images will be obtained using a gradient-recalled echo planar imaging sequence with the following parameters: TR/TE = 2000/30 ms, FOV = 220 × 220 mm^2^, flip angle = 90°, matrix size = 64 × 64, 43 transverse slices without slice gap, voxel size = 3.75 × 3.75 × 3.2 mm^3^, and a total of 266 volumes for each subject.

MRI will be performed during the periovulatory phase (days 12–16 of the menstrual cycle) [47, 48]. All participants will be free from a typical migraine attack for, at least, 1 week prior to the MRI scan [47]. During the examination, subjects will be instructed to lie down with their eyes closed, not to think of anything, and particularly not to fall asleep. Foam padding will be used to restrict head motion, and earplugs will be used to attenuate scanner noise.

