#### 2.6.1. Acupuncture Group

In the acupuncture group, the needles will be placed at obligatory acupoints Fengchi (GB20), Shuaigu (GB8), and Baihui (DU20) in all treatments. Using syndrome differentiation, acupoints from other meridians will be chosen according to the location of headache as follows: Shaoyang headache: Waiguan (SJ5) and Yanglingquan (GB34); Taiyang headache: Kunlun (BL60) and Houxi (SI3); Yangming headache: Hegu (LI4) and Neiting (ST44); and Jueyin headache: Taichong (LR3) and Neiguan (PC6) (Table 2 and Figure 2). Except DU20, other acupoints will be selected bilaterally in this prescription. Acupoints other than the prescribed ones will not be used. The treatment strategy is based on experience from our previous study and consensus meetings with clinical experts [33]. Disposable sterile acupuncture needles (25 to 40 mm in length and 0.25 mm in diameter) will be used in the treatment. Each point will be needled to achieve the Deqi sensation, and needles will be retained for 30 minutes per session. Patients will receive 12 sessions of manual acupuncture treatment (once every other day to a total of three times per week, followed by a 2-day break) for a period of 4 weeks. Treatments will be performed by licensed acupuncturists who have received more than 3 years of training.

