#### 2.6.2. Control Group

In the control group, flunarizine (manufacturer: Chongqing Kerui Pharmaceutical Co., LTD., Chongqing, China; SFDA approval number: H19994054) will be administered at a dose of 5 mg daily, following migraine guidelines and the professional advice of neurologists [22–25]. Patients will take the capsules continuously for 4 weeks without interruption.

In principle, participants should not take any analgesic medication during the study period. However, ibuprofen sustained-release capsule (Manufacturer: Tianjin Smith Kline & French laboratories, LTD., Tianjin, China; SFDA approval number: H20013062) can be taken as a rescue medicine for unbearable headaches, but the usage must be recorded in the headache diary.

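### Stool storage route is left to patient preference and is not held constant over time, so handling can add noise to microbiota change and could differ by arm, most plausibly at week 4

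*Protocol article*

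**What the plan says.** Section 2.4.2 (Gut Microbiota Collection) lets the patient decide where the sample is taken: "the collection sites can be selected at home or in the hospital", as the patient prefers. Storage follows from that decision. A hospital sample is "immediately frozen at −80°C in the hospital". A home sample may be "briefly stored in a domestic refrigerator at 4°C before being transferred to researchers within 24 hours". The same section links stool to imaging: "The collection time of the fecal sample will be ±1 days for MRI examination". Section 2.4.3 places the scanner "in the Hospital of Chengdu University of TCM", for both arms.

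Table 1 schedules stool and MRI at weeks 0, 4 and 16. Contact during treatment differs by arm. In section 2.6.1, "Patients will receive 12 sessions of manual acupuncture treatment", three per week over four weeks, and the place of treatment is not stated. In section 2.6.2, "Patients will take the capsules continuously for 4 weeks without interruption", and no treatment visits are described. Section 2.5.3 accepts that double-blinding is difficult. Section 2.9.2 plans diversity indices and ordination by group and mentions neither collection site nor storage route.

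**The concern.** The article sets an explicit rule that allows two pre-analytical routes and lets the participant pick between them. It does not tie the choice to the patient's earlier choice. At weeks 4 and 16 the patient can choose while knowing the allocated treatment.

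Two things could follow. First, if the routes give different readings, a patient who switches between visits has a change score that contains the handling difference as well as any biological change. Second, if the share of home samples differs between arms after treatment, the handling difference becomes part of the between-arm comparison. Randomisation does not balance a choice made after it.

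The second objective in section 2.1 is to compare gut microbiota between arms, and the third is to correlate microbiota with symptoms and brain activity. Both, together with the tripartite network in section 2.9.4, rest on these samples.

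**Working it through.** **Step 1. The number per arm.** Section 2.5.1 assumes changes of 4.1 ± 3.5 and 1.9 ± 2.3, α = 0.05 and power 0.80. Section 2.9.1 makes tests two-sided.

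- SD = √[(3.5² + 2.3²)/2] = √8.77 = 2.961
- d = (4.1 − 1.9)/2.961 = 0.743
- Exact t-test power is 0.794 at 29 per arm and 0.808 at 30 per arm.

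The stated 30 per arm reproduces. It serves here only as the number of samples per arm.

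**Step 2. When could handling follow the arm?**

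| Sample | Treatment sessions nearby | Hospital MRI within ±1 day |
|---|---|---|
| Week 0 | None yet, either arm | Both arms |
| Week 4 | Acupuncture arm only, place not stated | Both arms |
| Week 16 | None, either arm | Both arms |

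Routine contact differs between arms around week 4 only. The ±1-day window means that a sample need not be produced at the MRI visit, and even on that day the patient may collect at home.

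**Step 3. Size under assumptions.** The article gives no handling effect and no route shares, so both are assumed. Let h be the shift in an index caused by home handling, in units of the within-route SD. Let p_A and p_F be the shares of home samples in the acupuncture and flunarizine arms. With no true treatment effect:

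- Spurious difference: b = h × (p_F − p_A)
- Variance within arms, averaged: v = 1 + h² × [p_A(1 − p_A) + p_F(1 − p_F)]/2
- Noncentrality: (b/√v) × √(30/2), with 58 degrees of freedom

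Worked example: h = 1, p_A = 0.3, p_F = 0.7. Then b = 0.4, v = 1 + (0.21 + 0.21)/2 = 1.21 and √v = 1.1. The noncentrality is (0.4/1.1) × 3.873 = 1.41, and the test rejects in 28.3% of trials.

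False-positive rate of a two-sided 5% t-test, 30 per arm:

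| Home shares (acupuncture vs flunarizine) | h = 0.25 | h = 0.5 | h = 1.0 |
|---|---|---|---|
| 50% vs 50% | 5% | 5% | 5% |
| 40% vs 60% | 5.4% | 6.6% | 10.5% |
| 30% vs 70% | 6.7% | 11.5% | 28.3% |

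The distortion is material only when the shift and the imbalance are both sizeable. The variance term matters: leaving it out gives 33.2% instead of 28.3% in the last cell, because mixed handling also widens the spread within each arm.

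**Step 4. Change scores.** If the shift is additive, the spurious difference in change from baseline is h × [(p_F − p_A) at week 4 − (p_F − p_A) at baseline]. If every patient stays on the baseline route, the two terms are equal and this difference is 0. If patients switch equally often and in the same directions in both arms, it is also 0 on average, but each switch still adds ±h to that patient's change.

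**The case against.** A reader might infer that handling will differ by arm because only acupuncture patients come to the hospital regularly. The article does not support that. It does not say where acupuncture is given, so hospital treatment visits are an inference. Every stool sample in both arms falls within a day of an MRI at the same hospital, so access to hospital collection is similar when samples are due. The scan date is tied in section 2.4.3 to menstrual-cycle days and to an attack-free week, and no link to the treatment timetable is stated. The mechanism also reaches only one of the three samples. All of this stands, and it reduces a presumed bias to a possible one.

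A reader might also take the larger false-positive rates as an estimate of harm. They are not one. The shift and the shares are both assumed, and modest values leave the rate close to 5%. Storage at 4°C is described as brief, with 24 hours as the limit. A stool storage kit is named, but the article does not say whether it stabilises the sample.

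Finally, recording and adjusting for route are details that a sample procedure or analysis plan may hold, and section 2.7 refers to operating procedures. Their absence from an article is therefore not the point. The point is the rule that the article does state, which is free choice between two storage conditions. The objection does not remove that.

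**Conclusion.** The point holds as a limited, avoidable design weakness. Patient preference decides between two storage conditions, the article does not hold a patient to one of them, and the later choices can follow open-label allocation. Handling can therefore add noise to within-patient change and could differ by arm, most plausibly at week 4.

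The documents do not show that a difference between arms will occur or that the microbiota comparison is biased. Under the stated assumptions the false-positive rate runs from 5% (equal shares) through 5.4–10.5% (20-point imbalance) to 6.7–28% (40-point imbalance), for shifts of 0.25 to 1.0 SD. The consequence is confined to the microbiota results and the analyses built on them. The primary outcome, change in migraine attack frequency, is not affected.

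**What to change.** Preferred: replace patient preference in section 2.4.2 with one handling procedure for every sample, in both arms and at all three time points, with a common target time to freezing. A shared upper limit alone would not be enough, because refrigeration time could still vary from almost nothing to 24 hours.

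At the least: keep each patient on the route used at baseline, and record the route and the hours to freezing for every sample. Accompany the between-arm microbiota comparison with a sensitivity analysis adjusted for both. Adjustment fits a sensitivity analysis better than the main one, because the later routes can be chosen after randomisation.

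The cost is a change to the patient instructions, two fields on the sample form and slightly less convenience for patients. The change has to come before sampling, since handling that was not recorded may not be recoverable later.
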